### Planned analyses

#### Analysis for aim 1

All analyses will be conducted on the full sample regardless of exposure to treatment (intent-to-treat). Our primary hypothesis in Aim 1 is that CET will be associated with greater improvements than SST in both the *primary outcome*: community functioning (SAS, QLS), and the *secondary outcomes* of neuro- and social cognition (BACS and MSCEIT) and social skills (SSPA). To test this hypothesis, we will fit generalized linear mixed-effects models (GLMM) with identity link functions and a normal distribution specification for both the primary outcome and the secondary outcomes (because both outcomes are measured with interval-level scales). Because patients are nested within site, and repeated observations are nested within participants, we will fit a 3-level mixed-effects model: treatment arm (CET vs SST), time (baseline, 6-, 12- and 18-month) and arm-by-time interactions will be specified as fixed effects. The primary hypothesis of interest will be examined by testing the significance of the difference from zero in the rate of improvement over 18 months (arm-by-time interaction effect). To consider possible variance inflation due to clustering at the site and patient level, site will be treated as a random effect, and the intercept and slope for time at patient level will be specified as random effects. Randomization of sites to implement the CET or SST intervention will be stratified by geographic proximity, such that pairs of sites closest to each other will be randomized to different treatment conditions, and by organizational type and demographic characteristics of the surrounding area. This stratification plan will minimize the impact of any potentially confounding effects on the findings related to the bases of stratification. Because use of stratification may induce correlation between treatment arms, as a recommended cautionary measure, we will adjust for this stratification by including it as a random effect [92].

Because the interventions will be delivered in a group format sequentially for both arms, therapeutic groups could be considered as another level of clustering to be adjusted. We therefore will also test for effects with a 3-level model that includes the 51 treatment groups as another level of clustering. If variability (random effects) at the therapeutic group level is not significant, or if there is no improvement in model fit, we will remove therapeutic group as another level of clustering and retain the 2-level model. Whether a 2- or 3-level model is the final one chosen, we will specify heterogeneity of group effects (treatment arms) in the model to account for any potential variation between the treatment groups.

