**Methods:**

The study uses a randomized cluster design in which a pair of clinicians at community- and hospital-based mental service centers deliver either CET or HOPES to at least one group of 6-8 eligible clients for 12 months. Clinicians are trained and then supervised weekly, with ongoing process measurement of treatment fidelity, attendance, satisfaction, and retention, and use of other services. Measures administered at baseline and at 6 and 12 months while in treatment, and then at 18 and 24 months after treatment include social adjustment, quality of life, social skills, positive and negative symptoms, and neuro- and social cognition. We hypothesize that CET will be associated with greater improvements than SST in both the primary outcome of community functioning and the secondary outcomes of neuro- and social cognition and social skills. Secondarily, we hypothesize that more cognitive impairment at baseline and younger age will predict more benefit from CET compared to HOPES.

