### Sample size and power

We expect that each treatment site will enroll on average about 16 participants, yielding a total of 378 participants (see Fig. 2). For all power analyses conducted, based on previous experience, we assumed 20% attrition by 12 months. We further assumed four assessment points (baseline, 6-, 12-, 18- and, for 75% of the sample, 24-month), an alpha level of 0.05, a two-tailed test, with a cross-time correlation of 0.5. We will minimize treatment dropout by reaching out to participants whenever they miss treatment sessions (through the site RA) and by providing makeup sessions (through the site clinicians) that allow those who have missed up to eight sessions to reengage in the treatment without missing content. We will minimize attrition from the research procedures by identifying multiple contact persons when enrolling each participant and by using multiple forms of outreach when a participant is not available for scheduling an assessment or misses a scheduled assessment. Based on our prior experience conducting clinical trials evaluating CET and HOPES (reviewed above), combined with our methods for minimizing attrition, we also believe it is realistic to estimate that the attrition rate for the 1-year durability follow-up will not exceed 20%. However, to be conservative we have estimated our power to detect significant differences between the groups based on a 25% attrition rate.

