Power analyses for Aim 1 were conducted using Diggle et al. [80] and Lu et al.’s [81] approaches implemented in the LongPower package [82] in R statistical software (version 3.52). Power calculations were conducted to determine minimum detectable differences between arms (CET vs. SST) in changes over time on the primary outcomes. The outcomes for primary hypotheses in Aim 1 are continuous. To detect significantly more improvement for participants in CET than SST with 80% power in the 2-level analysis, the adjusted sample size of N of 318 (with 20% attrition by 12 months) will detect a minimum effect size of 0.34, and the adjusted N of 274 will detect a minimum effect size of 0.37, respectively. Both detectable effect sizes are between small and medium according to Cohen’s d metric for effect size (0.2 = small, 0.5 = medium and 0.8 = large). For the 3-level analysis that includes adjustment for clustering at the therapeutic group level and the adjusted sample sizes of 302 and 252 (everything else is the same), the minimum effect sizes that can be detected are 0.35 and 0.38, respectively.

The full sample of 378 at baseline (thus ICC adjusted sample sizes of 318 and 274) will have 4 assessments (baseline, 6-, 12 and 18 months), but we will also collect data for 284 participants (75% of the original sample of 378) for one extra time point (baseline, 6-, 12-, 18 and 24 months) (thus an ICC adjusted effective sample size for *N* = 284 participants becomes 250—for an ICC of 0.01—and 222—for an ICC of 0.02—respectively, and so the detectable effect sizes with *N* = 250 and 222 with 20% attrition are 0.38 and 0.40, respectively. For the analysis with 3-level clustering (both site and therapeutic group, as well as participants over time), the adjusted sample sizes become *N* = 240 and 208 and the detectable effect sizes with 20% attrition are 0.39 and 0.42, respectively.

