#### Primary outcome measures

*Community functioning* is measured with the Social Adjustment Scale (SAS-II), which has previously been validated as an interview-based measure (utilizing self-reports) of social and community functioning [83]. The SAS-II quantifies adjustment in different roles (e.g., work, school), social and leisure activities, intimate relationships, and overall adjustment. *Quality of life* is assessed with the Quality of Life Scale [84]. This 21-question interview-based, interviewer-rated measure assesses social functioning, role functioning, and motivation, as indicated by items such as sense of purpose, curiosity, and inner drive [85]. To measure symptom severity, we will use a short, validated version of the Positive and Negative Syndrome Scale (PANSS-6, 6 items) [86, 87].

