#### Adjusting for multiple subgroup comparisons

Subgroup analysis for treatment effects (i.e., estimate of the treatment effect for each subgroup) is a common approach for HTE analysis, but it is susceptible to the issue of multiple post hoc analyses. For the analyses of primary and secondary hypotheses, it is necessary to control for possible Type I error due to multiple tests. However, our moderation analyses will test exploratory hypotheses, and thus we will report the results of statistical tests including both corrected and uncorrected probability levels. To this end, we will adjust the *p*-value to account for multiple tests for each subgroup analysis using the false discovery rate method [97] implemented in SAS software [98]. Subgroup analysis may also increase the likelihood of Type II error due to small sample sizes. Therefore, we will not rely on statistical tests and *p*-values alone to evaluate HTE; we will also examine estimated effect sizes (estimate divided by the standard deviation) and compute confidence intervals around these effect sizes.

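### The protocol article gives conflicting accounts of which scales are primary, and its stated power fits only a single test at two-sided 0.05

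*Protocol article*

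**What the plan says.** The protocol article describes the primary outcome in several places, and they do not agree.

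- **Abstract, Methods:** CET is expected to do better in "the primary outcome of community functioning and the secondary outcomes of neuro- and social cognition and social skills". The Aims and hypotheses section says the same. Both use the singular and name no scale.
- **Table 2:** community functioning is assigned to the SAS-II. The Heinrichs Quality of Life Scale has a separate role, quality of life, and the PANSS-6 has the role of negative symptoms.
- **Primary outcome measures:** three instruments appear under this heading. After the SAS-II and the Quality of Life Scale, the section adds that for symptom severity "we will use a short, validated version of the Positive and Negative Syndrome Scale (PANSS-6, 6 items") will be used. The PANSS-6 is absent from the section on secondary outcome measures.
- **Analysis for aim 1:** the primary outcome is "community functioning (SAS, QLS"). The PANSS-6 is not mentioned. The test is the arm-by-time interaction over 18 months, and it is not tied to one scale.
- **Power for aim 1 and the Aim 2 analysis:** both refer to primary outcomes in the plural. The Aim 2 text also treats community functioning and quality of life as two separate things.

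On error control, the section on multiple subgroup comparisons says of the primary and secondary hypotheses that "it is necessary to control for possible Type I error due to multiple tests". The one method it names, the false discovery rate, is for the subgroup analyses. The significance level appears once, among the power assumptions: "an alpha level of 0.05, a two-tailed test".

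**The concern.** A confirmatory comparison needs one answer to the question of which result decides the trial. Here the count is one, two or three scales depending on the section. The Aim 1 text, which governs the analysis, puts two scales inside one singular outcome without a rule for joining them.

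If CET is ahead on the SAS-II but not on the QLS, or the reverse, the article gives no reading of the result, and the choice of the deciding scale could be made after the data are seen. This is a head-to-head trial meant to guide treatment choice, so that would weaken its main conclusion.

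The power statement is affected too. If SAS and QLS are tested separately, the trial must give up either the 5% error rate or the stated 80% power. Only a single test, on one measure or one defined composite, keeps both.

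**Working it through.** **Inputs from the protocol article.** Two-sided alpha 0.05 and within-person correlation 0.5 ("an alpha level of 0.05, a two-tailed test, with a cross-time correlation of 0.5"); 80% power ("with 80% power in the 2-level analysis"); 20% attrition by 12 months; effective sample sizes 318 and 274 at site ICC 0.01 and 0.02 (302 and 252 when therapeutic group is added). At 318 the trial "will detect a minimum effect size of 0.34"; at 274 the figure is 0.37; at 302 and 252 the figures are 0.35 and 0.38.

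**Inputs that are assumed.** The pattern of retention on the way to 80%, and the correlation between test statistics on different scales. The article gives neither.

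**Step 1: reproduce the stated detectable effects.** For a repeated-measures model of the kind the article cites, with compound symmetry at 0.5,

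d = (z₀.₉₇₅ + z₀.₈₀) × √(4V/N), with z₀.₉₇₅ + z₀.₈₀ = 1.960 + 0.8416 = 2.8016.

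V is the variance factor from the retention-weighted information matrix. It is 1.176 for retention 1, 0.9, 0.8 and 1.169 for retention 1, 0.93, 0.87, 0.80.

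| Effective N | Computed d | Stated d |
|---|---|---|
| 318 | 0.340–0.341 | 0.34 |
| 274 | 0.366–0.367 | 0.37 |
| 302 | 0.349–0.350 | 0.35 |
| 252 | 0.382–0.383 | 0.38 |

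Cruder formulas at the same alpha come close. A comparison of two means with N × 0.8 gives 0.351 and 0.378 for N = 318 and 274, and a four-visit slope formula gives 0.333 and 0.359. With the article's own inputs, the stated effects are therefore those of one test at the full 0.05, with no share of alpha set aside.

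**Step 2: either scale sufficient, each at 0.05.** For k independent tests the familywise error is 1 − 0.95ᵏ. This is also the ceiling for jointly normal two-sided tests. Values at positive correlation are simulated.

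| Assumed correlation | SAS and QLS (k = 2) | With PANSS-6 (k = 3) |
|---|---|---|
| 0 | 1 − 0.95² = 9.75% | 1 − 0.95³ = 14.26% |
| 0.3 | 9.5% | 13.6% |
| 0.5 | 9.1% | 12.5% |
| 0.7 | 8.4% | 10.9% |

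**Step 3: both scales required.** Type I error is not inflated. If each scale alone has 80% power, joint power is 0.80² = 64% at correlation 0, 69% at 0.5 and 71% at 0.7.

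**Step 4: alpha shared between two scales.** At 0.025 per scale the detectable effect grows by (2.2414 + 0.8416)/2.8016 = 1.100.

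- 0.34 × 1.100 = 0.374 and 0.37 × 1.100 = 0.407, so about 0.37 and 0.41.
- With therapeutic group included, 0.35 × 1.100 = 0.385 and 0.38 × 1.100 = 0.418.
- At the originally stated effects, power per scale is Φ(2.8016 − 2.2414) = Φ(0.560) = 71%.

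These are first-step (Bonferroni) values. Holm is never less powerful than that.

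**The case against.** The strongest reply is that this is a labelling fault in a condensed article. The model and the contrast are fixed, only the scale is unclear, and the multiplicity procedure may sit in the full protocol or analysis plan, which are not shown. Part of this stands. The absence of a named procedure for the primary family is not a fault in itself, and the article does acknowledge that control is needed.

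A reader might go further and infer that each scale is tested at 0.05 with no multiplicity rule, that a win on any of them counts, and that the false-positive rate is about 14%. The documents do not support that reading:

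- Alpha 0.05 is stated only as a power assumption, not as the level for each scale.
- No any-one-wins rule is stated, and the sentence on type I error points the other way.
- The 14.3% figure needs the PANSS-6 as a third tested primary measure. It is in neither the hypotheses nor the Aim 1 list. Its place under the primary heading looks like a labelling error.
- Zero correlation between SAS-II and QLS is unlikely, because the article describes both as covering social and role functioning. The 9.75% is therefore a ceiling.

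A reader might also infer that the SAS-II overall adjustment score is the implied primary. Overall adjustment is only one of the areas the article lists for that scale, and no passage selects it.

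The reply does not remove the contradiction. An article may leave detail to another document, but its sections should not disagree on what is primary. Any later plan would have to depart from at least one of them.

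**Conclusion.** The concern holds as an inconsistency in the definition of the primary outcome. It does not show a planned inflation of type I error. The abstract and aims, Table 2, the primary outcome measures section and the Aim 1 analysis cannot all be followed at once, and the Aim 1 text gives no rule for using SAS and QLS together.

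The size depends on which rule is meant. With either scale sufficient at 0.05, familywise error is at most 9.75%, and about 9% at correlation 0.5. With both required, joint power is about 64–69% for correlation 0 to 0.5. With alpha split, the detectable effects are about 0.37 and 0.41. With one primary measure, the stated figures stand unchanged. The between-scale correlations are assumptions, and the joint-power figures also assume that the true effect on each scale equals its detectable effect.

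**What to change.** Make Table 2, the primary outcome measures section and the Aim 1 analysis agree. The simplest course is to name one SAS-II score, chosen by the investigators before unblinding, as the sole primary outcome, and to list the QLS and PANSS-6 as secondary. This matches the singular wording of the abstract and aims, and 0.34 and 0.37 remain valid.

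If SAS and QLS are both kept as primary, say whether either suffices or both are needed. Where either suffices, apply Holm at a total two-sided 0.05 and restate the detectable effects at 0.025 as about 0.37 and 0.41. Where both are needed, report the joint power in place of 80%. In either case, name the procedure that meets the article's own statement that error control is needed for the primary hypotheses, or refer to the document that contains it.

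The cost is wording in a few places. The price is that the QLS loses primary status or, if both scales stay with alpha shared, that the detectable effect is about 10% larger.

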#### Analysis for Aim2 (HTE or moderation effect)

We will explore differential effectiveness of the two interventions by baseline cognitive functioning and age. Prior research suggests that these factors may influence effectiveness of CET and SST in different ways, but the evidence is not strong, and no studies have been conducted of both treatments. Therefore, we consider these hypotheses exploratory rather than confirmatory in nature. Prior to modeling, two moderators, baseline cognitive impairment and age will be recoded into two dichotomous variables using a median split, respectively.

In this aim, we test heterogeneity of treatment effects (HTE) or moderation effects by fitting the interaction models and conducting sub-group analyses. To test HTE, we will use the same analytic models—GLMM for Aim 1—but we will include 3-way interaction terms (arm*time*group) in the model. A significant 3-way interaction effect will indicate the existence of the heterogeneity of treatment effects between subgroups. Following this step, we will conduct simple effect analysis to estimate treatment effect differences (a difference in slopes by time effect between arms) within each subgroup.

Conceptually, the secondary outcomes of neurocognition and social cognition can be viewed as an intermediated outcome (mediator, M). The intervention (X) may affect the primary outcomes (Y) indirectly through a pathway of the mediator (M) as illustrated in Fig. 1. To test the mediated effect (or mechanism of change), we will conduct causal mediation analysis within the counterfactual framework [93, 94]. The moderation hypothesis in Aim 2 may also apply to the mediation effect. That is, the magnitude of the mediated treatment effect may also vary depending on age category (young vs. old) and pretreatment cognitive functioning (high vs. low), thus we will also conduct moderated causal mediation analysis by treating age and baseline cognitive function as moderators (MO).

Specifically, we will compute change scores (amount of improvement) from baseline to 18 months (for all subjects), and from baseline to 24 months (for 3/4 of subjects) for both primary outcomes and mediators for mediation analysis. For primary (or marginal) mediation analyses, we will estimate total effect of the treatment (TE), which can be decomposed into direct treatment effect (called natural direct effect, NDE) and indirect (or mediated) effect (called natural indirect effect, NIE); that is, TE = NDE + NIE with two-way decomposition. Bootstrap methods will be used to estimate standard errors and confidence intervals for mediation effects. A major advantage of the causal mediation method is that it allows testing and controlling for potential confounding effects due to non-random assignments of the mediators. With this approach, the percentage mediated effect can also be calculated. To test mediated effects potentially moderated by baseline cognitive function (high vs. low) and age category (young vs. old), moderated causal mediation analysis will be conducted to examine whether mediation patterns are the same for subgroups defined by moderators. Magnitude and percent of mediated effect between the subgroups (conditional causal mediation effect) will be compared.

Variation between our patients and across our treatment delivery sites in patient engagement may also influence the effectiveness of both interventions. We expect that greater treatment dose (sessions attended) will multiply gains in treatment impact on community functioning and quality of life for both CET and SST, thus moderating the impact of treatment along both primary causal pathways, but not changing predictions of the relative effectiveness of CET compared to SST.

As our HTE analyses are not based on testing explanatory hypotheses, we will report the corresponding *p*-values for hypothesis testing for these subgroup analyses. However, rather than relying on statistical significance testing alone, we will evaluate HTE using a combination of statistical significance and clinically meaningful difference with emphasis on the magnitude of treatment effects with standard errors (clinically meaningful effect sizes) as outlined in PCORI Methodology Standards [95] and recommended by statisticians [96].

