### Eligibility and randomization

Potential participants are eligible if the referring clinician reports a DSM-5 diagnosis of schizophrenia, schizoaffective disorder, or schizophreniform disorder that is confirmed by a Mini International Neuropsychiatric Interview (MINI) for Psychotic Disorders Studies [77] administered via video conference by the project research coordinator. Participants must also be 18-65 years of age and have an estimated premorbid IQ > 70 (determined with the Wechsler Test of Adult Reading) and have no known organic neurological disease or intellectual disability (DSM-5). Prior to assessment, on-site research assistants review the project with potential participants and invite their participation if they sign a site- and treatment-specific Informed Consent Form.

Assessments of symptom severity, social cognition, and community functioning will be conducted via video conference by trained research assistants at the coordinating site, Beth Israel Deaconess Medical Center (BIDMC), who are blind to treatment condition. Treatment fidelity will be assessed by coding at least 10 recorded group therapy sessions each year for each treatment site, with 6 sessions in the first 3 months used for feedback and training and 4 or more at random intervals after that. Site research assistants will record participant attendance and engagement during group sessions.

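### Aim 2 splits age and baseline cognition at the sample median before modelling; if moderation is roughly linear, about a quarter to a third of the information is lost without need

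*Protocol article*

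**What the plan says.** The protocol article, section Analysis for Aim2 (HTE or moderation effect), fixes the coding of both moderators ahead of any model: "baseline cognitive impairment and age will be recoded into two dichotomous variables using a median split, respectively". The moderation test extends the Aim 1 mixed model: "we will include 3-way interaction terms (arm*time*group) in the model". Here group is the median-split variable. Treatment effects are then estimated within each half.

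The same halves carry over to the mediation work, where the text introduces moderated causal mediation with "To test mediated effects potentially moderated by baseline cognitive function (high vs. low) and age category (young vs. old" as its categories. The article describes no analysis with a continuous moderator and fixes no age or cognitive score as a cut-point.

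The hypothesis itself, in the abstract's Methods paragraph, is that "more cognitive impairment at baseline and younger age will predict more benefit from CET compared to HOPES". The section also sets the status of the aim: "Therefore, we consider these hypotheses exploratory rather than confirmatory in nature".

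**The concern.** Age and a cognitive score are measured on graded scales, and the predictions say more or less of each, not above or below some point. Splitting at the median tests a different proposition: that the CET-HOPES difference is constant within each half and jumps at a point set by whoever enrols. Two patients just either side of the median count as opposites, while an 18-year-old and someone just under the median age count as the same.

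What is at stake is the sensitivity of the moderation analysis and the usefulness of its result. The article presents Aim 2 as helping clinicians decide whom to refer to which treatment. A test that gives up information before modelling is more likely to miss a real gradient. The subgroup estimates it yields are averages over wide bands.

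**Working it through.** **Inputs from the protocol article.** Sample size and power gives "an alpha level of 0.05, a two-tailed test, with a cross-time correlation of 0.5", 20% attrition by 12 months, 378 patients, and effective sizes of 318 (ICC 0.01) and 274 (ICC 0.02). Power for Aim 1 gives minimum detectable effects of 0.34 and 0.37 at 80% power. Eligibility gives the age range: "Participants must also be 18-65 years of age". No power figure is given for Aim 2, and no distribution for either moderator.

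**Step 1: reproduce the stated Aim 1 figures.** Detectable effect = (1.960 + 0.842) × √(4φ/N). Here φ is the variance inflation at the last of four visits under exchangeable correlation 0.5, with retention falling linearly to 80%. This gives φ = 1.169.
- N = 318: 2.802 × √(4 × 1.169/318) = 0.340 (stated 0.34).
- N = 274: 2.802 × √(4 × 1.169/274) = 0.366 (stated 0.37).

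The stated figures reproduce, so the same set-up can be used for Aim 2.

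**Step 2: efficiency of the split, assuming linear moderation.** Relative efficiency = squared correlation between the moderator and its above-median indicator.
- Uniform: 3/4 = 0.75, a loss of 25%. This equals analysing about 378 × 0.75 ≈ 283 patients.
- Normal: 2/π = 0.637, a loss of 36%. This equals about 378 × 0.637 ≈ 241 patients.
- Other assumed shapes: a normal truncated to 18–65 (mean 42, SD 12–14) loses 31–32%, a bimodal age distribution about 20%, and strongly skewed moderators about 49–52%.

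**Step 3: power.** For a test with 80% power on the continuous scale, power after the split = Φ(2.802 × √RE − 1.960).
- Uniform: Φ(2.802 × 0.866 − 1.960) = Φ(0.466) = 68%.
- Normal: Φ(2.802 × 0.798 − 1.960) = Φ(0.275) = 61%.

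**Step 4: simulation check.** The arm-by-moderator interaction was simulated with 378 patients, 24 sites and ICC 0.02, fitted by generalised least squares with a site effect. Relative efficiency was 0.749 for a uniform moderator (power 85% to 72%) and 0.631 for a normal one (83% to 64%). When the true effect was instead a step at the median, the split was the better coding, with relative efficiency 1.29 (uniform) and 1.50 (normal).

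**Step 5: detectable difference between the two halves.** Age and cognition are taken to vary between patients within a site, so the shared site effect largely cancels from the interaction. With 24 sites of 16 and ICC 0.02, clustering multiplied the interaction standard error by 0.998 and the main-effect standard error by 1.14. The natural base is therefore N = 378.
- Main-effect scale: 2.802 × √(4 × 1.169/378) = 0.312.
- Difference between two halves: 2 × 0.312 ≈ 0.62 SD.
- Same contrast from a continuous normal moderator: 0.62 × √0.637 ≈ 0.50 SD.

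The part due to the split is the gap between 0.62 and 0.50. The rest is the ordinary cost of testing an interaction.

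**The case against.** The best defence is that Aim 2 is declared exploratory, and the article does not lean on significance alone. It judges heterogeneity by magnitude and clinical meaning, reports corrected and uncorrected p-values, adds effect sizes with confidence intervals, and admits the risk of Type II error in subgroups. All of that stands, and it limits the harm of a non-significant interaction. It describes the imprecision, though, and does not restore information dropped before the model is fitted. A continuous sensitivity analysis may exist in a document not shown, but the article states the split as the coding for the analysis itself.

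It is also fair that the hypotheses give direction, not a straight line. Linearity is therefore an assumption of this check. Yet the article proposes no step either, and a step at the median is the case in which the split was the more efficient coding.

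Some stronger conclusions are tempting and are not supported:
- **That 25–36% is a fixed loss.** It depends on linearity and on moderator shapes that the article does not give.
- **That the detectable subgroup difference is 0.68–0.73 SD.** Doubling the Aim 1 figures at N = 318 and 274 gives this, but it applies a deflation for site clustering that largely cancels from a within-site interaction. Most of any such figure would also remain after the fix.
- **That this is the weakest-powered test in the trial.** No Aim 2 power is stated, and the moderated mediation may be as demanding.
- **That the cut-point cannot be used in another clinic.** A reported median age is readable anywhere, and its sampling error is only about 1.2–1.4 years if age is uniform on 18–65. The cut-point depends on the sample, but failure to transfer is not shown. Sample percentiles would be sample-dependent in the same way.

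**Conclusion.** The point holds. The article fixes a coding that does not match its own directional hypotheses and that, under roughly linear moderation, gives up about 25% (uniform) to 36% (normal) of the information, or about 20% to 50% over the wider set of assumed shapes. Power of 80% becomes about 68% or 61%. The detectable subgroup difference is about 0.62 SD instead of an equivalent 0.50 SD, given the Aim 1 assumptions, 378 patients, moderators that vary within sites and, for the 0.50, a normal moderator.

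The weight is moderate. The aim is exploratory, and a reader should not infer any defect in the Aim 1 comparison, which does not use the split.

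**What to change.** Make arm by time by moderator the Aim 2 test, with centred continuous age and continuous baseline cognition. Check non-linearity, for example with a spline. Report the CET-HOPES difference with its confidence interval at moderator values fixed in advance, as stated ages and stated cognitive scores and not as percentiles of the enrolled sample. Keep the median split for descriptive display only, and use the continuous moderators in the moderated mediation as well.

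The cost is a change of analysis wording. Age and the cognitive scores are available on their original scales before any recoding, so no extra data, visits or patients are needed.
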